## Introduction

Prone positioning has become an increasingly common approach for thoracoscopic esophageal cancer surgery to facilitate surgical exposure. It has been associated with better surgical outcomes and improved perioperative safety compared to the classical lateral decubitus position [1]; however, it may significantly impact ventilation. Partial lung collapse and intrathoracic insufflation of carbon dioxide (CO₂), commonly used in these procedures, may contribute to significant alterations in respiratory physiology and acid-base balance.

Clinically, elevations in serum potassium levels associated with acute respiratory acidosis are often observed during these surgeries. While acidosis is generally known to affect potassium distribution, respiratory acidosis is typically considered to cause only minimal or no elevation in serum potassium compared to metabolic acidosis [2–3]. However, recent clinical reports challenge this view in the setting of critical illness; for instance, Pathak and Nanda described cases of severe, refractory hyperkalemia in COVID-19 patients where acute respiratory acidosis was identified as a major contributing factor [4]. Nevertheless, the combination of prone positioning, ventilatory compromise, and CO₂ insufflation may alter the expected physiological response.

The primary aim of this study is to quantify the magnitude of serum potassium elevation associated with acute respiratory acidosis during prone-position esophagectomy. Furthermore, we aim to explore the physiological drivers of this phenomenon, including the respective contributions of respiratory and metabolic factors. Ultimately, this research may contribute to enhancing the safety of ventilation strategies and optimizing electrolyte management for these complex procedures.

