### Outcomes

#### Primary outcome.

The mean difference in serum potassium levels between the baseline (supine) and the intraoperative (prone) timepoints.

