### Sample size estimation

The sample size calculation is based on the study’s primary outcome: the mean difference in serum potassium levels within the prone-position cohort. Our preliminary data from 50 cases indicate that serum potassium concentration increases by a mean of 0.73 mmol/L (standard deviation [SD] 0.53) during the prone phase. While this large effect size would allow for statistical significance with a very small sample, we aimed to power the study to detect a more conservative, yet still clinically significant, difference of 0.5 mmol/L. Although the precise threshold for adverse cardiovascular effects associated with an acute potassium increase remains undefined, the relationship between serum potassium and cardiovascular events typically follows a U-shaped curve [5]. Recent evidence further suggests that the magnitude of potassium increase is a significant predictor of arrhythmias [6]. Therefore, in the clinical setting of esophagectomy, we considered a 0.5 mmol/L increase to be a clinically relevant safety margin. Assuming a paired t-test with a two-sided alpha of 0.05 and a power of 80%, a minimum of 34 patients in the prone-position cohort is required.

We plan to include all eligible patients from both institutions within the study period (January 2022 - December 2024), targeting a total sample size of approximately 150 cases. While the primary power calculation is met with 34 patients, this larger sample size will provide robust data for the secondary outcomes, including the multivariable regression analyses, ensuring greater precision and the ability to explore multiple predictor variables.

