### Statistical analysis

The selection of the blood gas sample with the lowest pH during the intervention phase is a pre-specified criterion. This approach is not considered a selection bias but is rather a deliberate strategy to focus the analysis on the study’s primary research question: the physiological response, particularly in potassium homeostasis, to the most severe degree of acute acidosis encountered during the procedure.

All statistical analyses will be performed using R version 4.3.2 (R Foundation for Statistical Computing, Vienna, Austria). A p-value of less than 0.05 will be considered statistically significant.

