#### Analysis for the primary outcome.

A paired t-test will be used to compare the mean serum potassium levels between the baseline and intraoperative timepoints.

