## Discussion

This study protocol was designed to address a critical clinical observation: a greater-than-expected elevation in serum potassium during prone-position esophagectomy. This finding stands in contrast to the conventional physiological understanding that respiratory acidosis—a common consequence of this procedure—causes minimal or no elevation in serum potassium, particularly when compared to metabolic acidosis [2–3]. Therefore, the primary objective of this study is first to confirm and quantify the mean increase in serum potassium between the supine (baseline) and prone-position phases. Given that acute respiratory acidosis is an almost inevitable event during this surgical phase, demonstrating a statistically significant potassium increase would, in itself, strongly suggest a clinically relevant phenomenon that challenges existing knowledge. However, we recognize that major surgery introduces multiple confounding variables that could influence potassium levels, such as metabolic stress. To address this complexity, our secondary analyses are designed to (1) assess the robustness of our primary finding via sensitivity analysis that controls for the effect of metabolic acidosis, and (2) explore the association between the potassium increase and various physiological drivers, including the severity of respiratory acidosis itself.

In particular, surgical techniques involving partial lung collapse and intrathoracic CO₂ insufflation may lead to rapid external CO₂ loading, resulting in acid-base changes distinct from those seen in endogenous respiratory acidosis. Multiple mechanisms, including H⁺/K⁺ exchange and altered ATPase activity, may contribute to this response. The body’s compensatory systems may not be able to fully respond to the acute rise in PaCO₂, potentially leading to more pronounced potassium fluctuations than typically expected.

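### The Discussion reads statistical significance against zero as clinical relevance, although at about 150 patients a mean rise one sixth of the protocol's own 0.5 mmol/L margin would be significant

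*Protocol article*

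**What the plan says.** All of the following is in the protocol article.

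- **Primary outcome:** "The mean difference in serum potassium levels between the baseline (supine) and the intraoperative (prone) timepoints".
- **Analysis for the primary outcome:** "A paired t-test will be used to compare the mean serum potassium levels between the baseline and intraoperative timepoints". No non-zero null value is given, so the hypothesis tested is a mean change of zero.
- **Statistical analysis:** "A p-value of less than 0.05 will be considered statistically significant".
- **Sample size estimation:** "we considered a 0.5 mmol/L increase to be a clinically relevant safety margin". The section sizes the study to detect that difference, admits that the exact threshold for cardiovascular harm is not known, and targets about 150 cases.
- **Introduction:** the view under challenge is that "respiratory acidosis is typically considered to cause only minimal or no elevation in serum potassium". The Discussion describes it in the same way.
- **Discussion, interpretation:** "demonstrating a statistically significant potassium increase would, in itself, strongly suggest a clinically relevant phenomenon that challenges existing knowledge". A later paragraph again makes confirmation of a significant increase the ground for a strong statement about monitoring.

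No section compares the estimate or its confidence interval with 0.5 mmol/L.

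**The concern.** Three parts of the protocol do not fit together. The test asks whether the mean change differs from zero. The view to be challenged allows a small rise. The protocol's own yardstick for relevance is 0.5 mmol/L. Rejecting zero neither contradicts a minimal rise nor shows that the rise reaches 0.5 mmol/L, yet the Discussion treats rejection as enough for both conclusions.

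At stake is what the study may claim. The protocol is published ahead of data access in order to fix the analysis plan. A reading announced there and tied to p<0.05 would allow a rise well below the protocol's own margin to be presented as clinically relevant and as contrary to accepted physiology. The Discussion extends the expected findings to monitoring and to permissive hypercapnia, so the inference carries weight beyond the primary table.

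**Working it through.** **Inputs.** SD of the change 0.53 mmol/L and preliminary mean 0.73 mmol/L in 50 cases (Sample size estimation: "increases by a mean of 0.73 mmol/L (standard deviation [SD] 0.53) during the prone phase"); target n about 150, two-sided alpha 0.05 and relevance margin 0.5 mmol/L (same section). I read 0.53 as the SD of the within-patient change, the natural reading of that sentence.

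**The plan's own figure.** The section states: "Assuming a paired t-test with a two-sided alpha of 0.05 and a power of 80%, a minimum of 34 patients". With a difference of 0.5 and SD 0.53, the normal approximation gives n = (0.53 × (1.960 + 0.842) / 0.5)² = 8.8, so 9, and the exact paired t calculation gives 11. The stated 34 is not reproduced. It is reproduced with SD = 1.0 (power 80.8%), that is, with 0.5 used as a standardised effect. That is a separate matter and adds no weight here, but it is why SD 1.0 is included in the range below.

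**Smallest significant mean at n = 150.**

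- SE = 0.53 / √150 = 0.0433 mmol/L.
- Critical value t(0.975, 149) = 1.976.
- Smallest significant observed mean = 1.976 × 0.0433 = 0.0855 mmol/L.
- Against the margin: 0.5 / 0.0855 = 5.8, so about one sixth.

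An observed mean of 0.09 would give p = 0.039 and a 95% CI of 0.004 to 0.176, which lies wholly below 0.5. These are observed means; the true rise detectable with 80% power is 0.122 mmol/L.

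**Dependence on the assumptions.**

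| n | SD | Smallest significant mean (mmol/L) |
|---|---|---|
| 150 | 0.40 | 0.065 |
| 150 | 0.53 | 0.086 |
| 150 | 0.70 | 0.113 |
| 150 | 1.0 | 0.161 |
| 100 | 0.53 | 0.105 |
| 50 | 0.53 | 0.151 |

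In every row the value is below one third of 0.5 mmol/L.

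**How likely a small result is.** The preliminary data give 0.73 ± t(0.975, 49) × 0.53/√50, a 95% CI of about 0.58 to 0.88. The lower limit lies (0.58 − 0.0855) / 0.0433, or about 11 standard errors of the planned study, above the smallest significant mean.

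**What reading the CI against 0.5 would give** (n = 150, SD 0.53, half-width 0.0855).

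- CI wholly above 0.5: observed mean above 0.5 + 0.0855 = 0.586.
- CI wholly below 0.5: observed mean below 0.5 − 0.0855 = 0.414.
- CI includes 0.5: observed mean between these two values.

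The chance that the CI lies wholly above 0.5 is 99.96% if the true mean is 0.73, 93% at 0.65, 79% at 0.62, 63% at 0.60, and about 2.5% at exactly 0.5.

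**The case against.** The best case for the protocol has four parts.

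1. The Methods contain no rule that equates significance with relevance. The sentence is Discussion prose, it is hedged, and the text that follows it raises confounding. This stands as a reason for lower severity. But the hedge is paired with wording that makes significance sufficient by itself, and the caveat concerns the cause of the rise, not its size.
2. The primary outcome is itself a mean difference, and the Discussion sets out to confirm and quantify it. This stands. A reader might infer that the plan fails its aim of measuring magnitude; the documents do not support that. Nor is the lack of an explicit CI in an article a finding, since such detail may sit in a document not shown.
3. A trivial result is remote given the preliminary data. This stands too. A reader might infer that the study is likely to report a trivial rise as important; the preliminary mean and its CI point the other way. An inference announced in advance must still be valid for results not yet known.
4. The 0.5 mmol/L is a difference to detect, and the protocol says the precise harm threshold is undefined. This limits the remedy. A reader might infer that the primary hypothesis must be replaced by a test against 0.5. That is a stricter and debatable criterion: an observed mean of 0.55 would fail it, and a true mean of exactly 0.5 would pass only about 2.5% of the time. The documents do not require it, and testing a paired change against zero while reporting its size is ordinary practice.

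**Conclusion.** The inference in the Discussion is invalid on the protocol's own terms. With about 150 patients and SD 0.53, significance is reached from an observed mean of about 0.086 mmol/L, one sixth of the stated margin, and such a rise would be compatible with a minimal elevation. The figure rests on the preliminary SD and the target n, but the conclusion holds for every SD from 0.40 to 1.0 at n = 150.

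The point is limited to interpretation. The paired design, the outcome and the t-test are sound, and on the preliminary data the mean may well exceed 0.5 mmol/L. Severity: should fix.

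**What to change.** 1. Keep the paired t-test. State that the primary result is the mean change with its 95% CI.
2. In the Discussion, remove the statement that significance alone indicates a clinically relevant phenomenon.
3. There, and in the later paragraph that draws on a significant increase, base any claim of relevance on where the estimate and its 95% CI lie relative to the pre-stated 0.5 mmol/L. A CI wholly above 0.5 supports a relevant mean rise, a CI wholly below does not, and a CI that includes 0.5 is inconclusive on that point.

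The cost is wording only, with no further data and no change to the sample. The downside is that a significant result may no longer support the relevance claim if the observed mean is near or below about 0.59 mmol/L. By the protocol's own timetable the statement was written before extraction and analysis; the change should be made before the results are known.
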